## **SUMMIT activity design and methodology**

*Outcomes:* The SUMMIT activity is a controlled trial designed to assess the relative impact of a prenatal multi-micronutrient tablet in comparison to the current MOH iron/folate tablet on frequency of maternal mortality as assessed by both the maternal mortality ratio (MMR), defined as maternal deaths per 100,000 live births, and the maternal mortality rate (MMRT), defined as the death of a woman while pregnant or within 42 days of termination of pregnancy from any cause aggravated or related to the pregnancy, expressed per 100,000 pregnancies. Two additional main outcomes of the SUMMIT activity are proportion of low birth weight infants, and infant mortality, including neonatal mortality. Secondary outcomes to be assessed include maternal morbidity, neonatal development, and nutritional status during pregnancy and lactation. In addition to examining the effect of multi-nutrients, we will document the effect of education and social marketing of the SUMMIT activity by comparing outcome rates in the iron/folate arm of the intervention area to corresponding rates in designated villages where standard prenatal care practice will continue. In a 20% subsample of pregnancies biochemical status for micronutrients, including, iron, zinc, and vitamin A, will be determined.

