*Sample Size:* The SUMMIT activity will aim to detect a reduction in both MMR and MMRT of at least 30% with a power of 80% and significance level of 0.05. Current estimates of the MMR in various districts on Lombok range from 400 to 800 maternal deaths per 100,000 live births and randomization for the trial will be by clusters consisting of geographic areas serviced by each of the 300 midwives providing prenatal care. Assuming 400 maternal deaths per 100,000 live births and a 10% loss to follow-up, the trial would require enrollment of 102,000 live birth pregnancies allocated to either an iron/folate or multinutrient supplement to detect a 30% reduction in MMR. Because not all pregnancies result in a live birth, it is estimated that the required sample size be increased an additional 15% to 120,000. This sample size will also allow detection of similar reductions in MMRT. It is proposed that enrollment be phased in over a 6-month period and continue for at least 2 years to accommodate seasonal effects. The phased in implementation along with the approximately 72,000 pregnancies occurring each year throughout the trial area yields a projected enrollment of 126,000 pregnancies. The additional margin of enrollment provides the ability to detect reductions in MMR as little as 22% if ratios approach 800 per 100,000 live births. With regard to low birth weight and infant mortality rates, the projected sample size will allow detection of at least a 10% reduction in low birth weight and infant mortality rates, including neonatal mortality rates. Equally important is determination of the impact of the social marketing and education programs that will accompany the trial implementation in the intervention area. Data concerning outcome variables in the absence of the intervention will be collected during the phase-in period prior to enrollment. This will result in the ability to detect at least a 25% difference in MMR between the iron/folate arm of the intervention area compared non-intervention areas.

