*Supplementation:* Pregnant women will be provided with either an iron and folate tablet or another multi-micronutrient tablet containing iron, folate, vitamins A, B1, B2, B6, B12, C, D, and E, along with niacin, zinc, copper, selenium, and iodine. Supplements will be provided by existing MOH midwives, and be distributed from the first antenatal consultation for a confirmed pregnancy until three months postpartum. The midwives will distribute the supplements monthly as 30-tablet sachets, as is current MOH practice, and monitor the health impact through routine prenatal care visits and compliance checks. Additional compliance monitoring will be conducted by HKI field workers through spot-checking of pill counts and biochemical indices.

*Monitoring:* In addition to the distribution of supplements, midwives will continue to record the results of routine prenatal examinations, attend deliveries and record data on labor and delivery, birth weight, and APGAR scores of neonates. All of these activities are currently part of the normal maternal care protocol implemented by the MOH. The implementation of these activities will be strengthened in all villages by training and community promotion. HKI field workers will collect additional data at enrollment, at 36 weeks of gestation, and at 12 weeks postpartum on socio-economic status, food intake, and anthropometry. Deaths will be detected through the longitudinal surveillance of participants and also through the quarterly island-wide demographic surveillance system. The dual surveillance will allow the trial to document all maternal deaths (up to and exceeding 12 weeks postpartum), to allow evaluation of MMR and MMRT, and all infant deaths occurring beyond the 12-week visit. Lastly, it will allow monitoring of mortality in the non-intervention villages. For all maternal and infant deaths verbal post-mortem assessments will be made to determine the associated causes and conditions.

*Implementation schedule:* The trial will be carried out over five years in 3 distinct stages broadly scheduled as follows; Phase I- Preparation and training from December 1999-August 2000, Phase II-Supplementation and follow-up from September 2000-September 2003, and Phase III-Analysis and report preparation from October 2003-October 2004.

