## **V. SUPPLEMENT DISTRIBUTION**

We propose to utilize the existing antenatal-care and maternal health information system as the mechanism for distributing the supplements and monitoring simple coverage rates. As mentioned above, supplements will be provided daily from the first prenatal consultation for a confirmed pregnancy through 90 days post-partum. The HKI intervention staff will provide additional detailed monitoring of compliance, and also work with the midwives to increase their knowledge of the importance of maternal nutrition and strengthen their capacity for distribution of supplements, record-keeping and monitoring. To avoid over-consumption of supplements, it will be carefully emphasized to midwives and pregnant women participating in SUMMIT that one tablet is to be taken daily, and that the supplement is in place of, and not in addition to, the normal MOH iron/folate supplement.

Use of the antenatal-care system will not only provide an opportunity for improvement of services in the area where the trial is being conducted, but will also provide valuable lessons learned for national policy and programming. Similarly, improving the existing health information system for impact monitoring will also strengthen the system. Importantly, independent monitoring of the system will be carried out by HKI to assess the reliability of the data obtained and for improving performance where necessary.

Importantly, the SUMMIT activity will not only provide information concerning the impact of micronutrients, but it will also assess the specific impact of activities accompanying the intervention such as promotion of prenatal care and social marketing. Evaluation of the relative individual effects of these factors as opposed to the multi-nutrient supplement itself will provide the basis for a cost-benefit analysis that will help the GOI to make informed decisions regarding health budget allocations. This evaluation will be achieved by first establishing a demographic surveillance system throughout the island so that district-specific maternal and infant mortality rates can be estimated. This will be followed by phased in prenatal care promotion and social marketing, and implementation of multiple micronutrient distribution.

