|                | 
In this phase, we will focus on preparations for the trial, including meetings with the appropriate provincial and district level MOH staff, community leaders and midwives. A field office will be established in Mataram, the capital of Lombok. Staff will be hired and trained. Survey protocols, field manuals and data collection forms will be designed and tested, and management systems will be put in place.
 
At the same time efforts to increase community links to the health care system will be conducted by development of appropriate social marketing
 |                           |

campaigns and educational materials to increase awareness within the community and demand for the supplements.

**Phase II**      Supplementation trial      September 2000-September 2003

Implementation of the double blind, community-based, cluster-randomized, controlled trial will start. Pregnant women will be enrolled for follow up over the course of pregnancy and until three months postpartum. Once the target number of pregnancies has been enrolled, enrollment will be discontinued. Women who have not yet delivered their babies will be followed until three months after delivery.

The design, sample size, and methods are detailed below (in Section B. Implementation methods).

**Phase III**      Analysis and Report Preparation      October 2003-October 2004

The study will produce a great deal of data, requiring extensive analysis. Scientific papers, reports and presentations of the findings will be made.

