## *5. Enrollment of pregnancies*

At the onset of the supplement distribution period, pregnant women reporting to a midwife or a midwife's assistant will be enrolled into the intervention if informed consent is given. When reported to the assistant, the woman will be referred to see the midwife as soon as possible. At the time of the first visit to the midwife, the pregnancy will be confirmed by means of a urine test, or physical examination, depending on the estimated gestational age. Based on existing midwife records, we anticipate that pregnancies will be reported between 3-5 months of gestation. Reporting may be earlier once the community knows about the urine test to confirm pregnancy and about the distribution of the supplements.

Because the trial relies exclusively on pregnant women actively seeking antenatal care from the village midwife, improved midwife-seeking behavior will be important. Before the start of the trial, the midwives will be motivated to recruit three to six women in their village to assist the midwife in her trial-related tasks. The role of these assistants is to facilitate identification and enrollment of pregnant women, distribute supplements, and report complications of delivery and maternal death to the midwife. A campaign to encourage early first visits to the midwives will also be conducted in the start-up phase of the trial. The purpose of this social marketing activity is to promote early first visits, promote the use of supplements and to promote the services of the village midwife and her assistants.

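### The protocol gives conflicting accounts of where and when promotion starts, so the comparator for the education and social-marketing effect is not protected from the programme it is meant to lack

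*Protocol*

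**What the plan says.** Besides the supplement comparison, the protocol sets out to measure the effect of the accompanying education and social marketing. The Executive Summary (Outcomes) compares the iron/folate arm with "designated villages where standard prenatal care practice will continue". Its Sample Size paragraph describes the object of evaluation as "the social marketing and education programs that will accompany the trial implementation in the intervention area". Section VIII.B.3 sizes this contrast at 54,000 non-intervention against 63,000 iron/folate pregnancies, with 20-25% detectable at 80% power. Section VIII.B.8 will also judge the effect of more midwife-attended births by comparing baseline with the iron/folate group. Section VIII.B.12 feeds the contrast into cost-benefit work.

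On timing, Section V sets up surveillance first and then says: "This will be followed by phased in prenatal care promotion and social marketing".

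Other statements point elsewhere:
- Executive Summary, Monitoring, after listing routine examinations, delivery attendance and birth records: "The implementation of these activities will be strengthened in all villages by training and community promotion".
- Section VIII.B.5, on assistants: "Before the start of the trial, the midwives will be motivated to recruit three to six women in their village".
- Section VIII.B.5, on promotion: "A campaign to encourage early first visits to the midwives will also be conducted in the start-up phase of the trial".

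**The concern.** The contrast is interpretable only if comparator pregnancies have not received the programme. If training and promotion reach all villages, or assistants and the campaign are in place before a village is phased in, part of the programme is already acting in the comparator. The contrast then measures only what is added later, and its bias is towards no effect. A useful promotion programme could be reported to the government as giving little or nothing, in an analysis meant to inform health budgets. Once the baseline months are exposed, no later analysis can recreate an unexposed comparator.

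**Working it through.** **1. Where the comparator comes from.** The protocol gives the total of 54,000 but not its make-up. The schedule reproduces it exactly:
- 72,000 pregnancies a year (VIII.B.1) is 6,000 a month.
- Baseline surveillance runs for 6 months (VIII.B.4): 6 × 6,000 = 36,000.
- Phase-in is by thirds at 3-month steps (VIII.B.2). Waiting villages contribute 3 × 4,000 + 3 × 2,000 = 18,000.
- Total: 36,000 + 18,000 = 54,000.
- Enrolment over 2 years: 144,000 − 18,000 = 126,000, or 63,000 per arm, as stated.

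So the comparator appears to consist of trial villages before their own phase-in. What separates it from the iron/folate arm is then timing.

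**2. Calendar.** Phase I runs from December 1999 to August 2000 and supplementation begins in September 2000 (VIII.A). If distribution starts then, baseline covers about March to August 2000, inside Phase I. Anything done in all villages before the trial starts can therefore fall in the baseline months.

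**3. The plan's detectable effect.** I used two-sided 0.05 (sidedness is not stated) and 80% power for 54,000 against 63,000. The detectable reduction without inflation is 24.3%, 20.0% and 17.5% at a maternal mortality ratio (MMR) of 400, 600 and 800 per 100,000. Dividing both groups by the protocol's allowances (1.2 for clustering, 1.1 for loss, 1.15 for non-live births; product 1.518) gives 29.4%, 24.4% and 21.3%. The stated 20-25% is thus reproduced in order of size, and it assumes an unexposed comparator.

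**4. Dilution.** Let e be the true reduction and f the share of it already acting in the comparator. The comparator rate is p(1 − fe) and the iron/folate rate is p(1 − e), so

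observed reduction = 1 − (1 − e)/(1 − fe).

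With e = 0.25:
- f = 0.25: 1 − 0.75/0.9375 = 20.0%
- f = 0.5: 1 − 0.75/0.875 = 14.3%
- f = 0.75: 1 − 0.75/0.8125 = 7.7%

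The documents give no f. One scenario can be tied to the schedule. If promotion reaches all villages only when distribution begins, and then acts fully, the exposed share is 18,000/54,000 = 1/3 and the observed reduction is 1 − 0.75/0.9167 = 18.2%. If it also covers the baseline months, f moves towards 1 and the contrast disappears.

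**5. Power.** At MMR 600 and e = 0.25, with groups of 54,000/1.518 = 35,573 and 63,000/1.518 = 41,502, power is:

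| f | Comparator / iron-folate rate per 100,000 | Observed reduction | Power |
|---|---|---|---|
| 0 | 600 / 450 | 25.0% | 0.82 |
| 1/3 | 550 / 450 | 18.2% | 0.50 |
| 1/2 | 525 / 450 | 14.3% | 0.32 |
| 2/3 | 500 / 450 | 10.0% | 0.17 |

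**The case against.** The best reply is that the protocol's explicit sequence protects the comparator. Section V puts promotion after surveillance is set up, and the Executive Summary places the programmes in the intervention area. The conflicting statements can be read to agree with this. All villages may mean all supplementing villages, since the same paragraph names non-intervention villages separately. Start-up may mean the stepwise launch, and a campaign that promotes supplement use fits a launch in each area. Most of the assistants' tasks presuppose distribution.

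These readings are possible, but the text does not choose them. The Monitoring sentence carries no date. Section VIII.B.5 does not say that recruitment is local to each third. Naming non-intervention villages separately also suggests that all villages includes them. Delivery attendance, one of the activities strengthened, is itself evaluated against baseline in Section VIII.B.8.

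Two parts of the reply stand. A reader might infer from Section VIII.A that campaigns are delivered in Phase I, but the text says "efforts to increase community links to the health care system will be conducted by development of appropriate social marketing", continuing with "campaigns and educational materials to increase awareness within the community and demand for the supplements". That describes developing materials, and doing so exposes nobody. A reader might also conclude that all 54,000 comparator pregnancies are contaminated. That needs the most adverse reading of every statement, against Section V.

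**Conclusion.** The concern holds as an unreconciled contradiction, not as proven contamination. The Monitoring paragraph and Section VIII.B.5, followed literally, would expose comparator villages and months that the Outcomes paragraph and Section V need unexposed, and would bias the programme contrast towards no effect. Under the assumed f of 0.25 to 0.75, a true 25% reduction would appear as 20% to 8%. The 36,000/18,000 split is an inference, although it reproduces the stated totals. The dilution and power figures are illustrations.

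It would be wrong to extend this to the main question. The multi-micronutrient versus iron/folate comparison is randomised and promotion reaches both arms, so it is not affected. The point should be settled before baseline surveillance starts.

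**What to change.** 1. Amend the Monitoring paragraph and Section VIII.B.5 to follow Section V: community promotion, the early-visit campaign, and assistant recruitment and incentives start in each village at its own phase-in date. Developing materials in Phase I can stay.
2. Keep training in data recording and verbal autopsy the same in all villages and periods. Midwives carry out the verbal autopsies (VIII.B.8, VIII.B.10) and the update training covers data collection (VIII.B.11). Delaying that training to phase-in would make death ascertainment differ between the comparator and the iron/folate arm.
3. Log the actual start date of each component in each village. Count outcome time as non-intervention only before that date, and censor or allocate the 42-day maternal and 12-month infant windows at it. Classifying by the date the pregnancy ended is not enough, because those windows can run into the exposed period.
4. If any component does start everywhere, limit the programme objective to the components actually phased in.

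Cost: promotion reaches the second and third waves 3-6 months later, one date log per village is needed, and the comparator may be somewhat smaller than 54,000.

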## **Relevance to MOH and USAID objectives**

The proposed maternal SUMMIT activity is directly in line with the USAID/I Mission's Strategic Objective, "Protecting the Health of the Most Vulnerable Women and Children". It also fully supports USAID/I's "Essential Services Component Two: Maternal and Neonatal Health (MNH)," by working through the existing health care system to assist in "maintaining and ultimately improving the quality and delivery of services that have proven effective in addressing the most important causes of maternal and neonatal morbidity and mortality." SUMMIT contributes directly to the Essential Package of Safe Motherhood Services, focused on improving the clinical skills of midwives for antenatal care and birthing practice for safe delivery; management of complications and timely referrals; identification of risk factors for neonatal mortality; care of normal and sick neonates; and postpartum care. It also strengthens "demand generation and community empowerment efforts to improve birth preparedness," and "the technical and management capacity" of midwives, and includes efforts to "improve the utilization of safe motherhood and child health services at the community level." SUMMIT also works toward "a decrease in the prevalence of anemia among pregnant women in project areas" (IR1: Essential Services Preserved) and an increase in the "percentage of adults knowledgeable about maternal complications of pregnancy and childbirth" (IR3: Promotion of Appropriate Behaviors and Services).

|              |                                                                                                             |           |
|--------------|-------------------------------------------------------------------------------------------------------------|-----------|
| I.    | INTRODUCTION.....                                                                                    | 3  |
| A.           | Background .....                                                                                            | 3         |
| B.           | Problem .....                                                                                               | 4         |
| II.   | CAUSES OF MATERNAL MORTALITY AND LINKS TO NUTRITION.....                                             | 7  |

## I. INTRODUCTION

### A. Background

Maternal and infant mortality remains an important public health problem in most developing countries. Both the maternal mortality ratio and infant mortality rates in Indonesia are among the highest in Southeast Asia. Despite great strides in reducing child mortality, reducing fertility and improving health status, rates for maternal, neonatal, and infant mortality remain remarkably high. There is a need for novel, cost-effective and targeted interventions to improve these health indicators. It is widely accepted that nutritional status, specifically micronutrient status, is one of the most important contributing factors to overall maternal health, birth outcome, and infant health. Indeed, the prevalence of micronutrient deficiencies remains high in developing countries, and pregnant and lactating women are among the most vulnerable because of their relatively high micronutrient requirements. Unfortunately, in most developing countries (where women's diets are marginal and health is poor) prenatal micronutrient supplementation is limited to the provision of iron/folate tablets. This contrasts sharply to the prevailing situation in developed countries (where women's diets and health are relatively good), where long-standing policies of routine antenatal care include multi-vitamin/mineral supplements.

The potential importance of poor prenatal micronutrient status is underscored by several studies in developing countries that demonstrate substantial benefits of micronutrient supplementation, including vitamin A, iron, zinc, and folate on maternal and infant health. The recent Nepal Nutrition Intervention Program-Sarlahi 2 (NNIPS-2) trial found that supplementation with vitamin A (retinol) or  $\beta$ -carotene among 45,000 women of reproductive age reduced pregnancy-related mortality by 40%. In addition, there is evidence from a variety of studies suggesting that other micronutrients given during pregnancy and lactation may contribute to the reduction of maternal and infant mortality. Health personnel worldwide are increasingly recognizing the positive impact of micronutrient supplementation on maternal and infant health, and the potential benefit of health programs focused on improving the micronutrient status of women during pregnancy and lactation.

Most of the above-mentioned nutrient intervention studies were aimed at measuring the impact of micronutrient supplements on maternal and infant health under rigorous conditions of supervised delivery and monitoring. To fully assess the programmatic potential of such interventions it is crucial to determine the *effectiveness* of micronutrient supplementation when delivered through existing antenatal care systems. The most informative setting to evaluate the programmatic effectiveness of pre-natal multi-micronutrient supplementation would include regions where strong government support exists for promoting maternal health. In this context, Indonesia provides an ideal venue to examine the impact of pre-natal multi-micronutrient supplementation on maternal and infant health.

Reduction of maternal mortality is a priority of the Ministry of Health (MOH) in Indonesia and a variety of program interventions have been implemented through the MOH Directorate General of Community Health and Directorate of Family Health. These are described in the *Strategies to Accelerate the Reduction of Maternal Mortality* and include a broad range of technical, management, and educational efforts intended to

improve obstetric services and referral systems, and to educate communities about maternal health issues.

The Indonesia Safe Motherhood initiative formally began in June 1988. This resulted in the “Healthy and Prosperous Mother Campaign” implemented in 1990 which included the training and placement of trained midwives (*bidan di desa*) in villages as a means to improve access to appropriate maternal care. These efforts were intended to be implemented through antenatal visits to the midwives and increased community awareness about the importance of maternal health for safe motherhood. With respect to nutritional status, the strategy included “efforts to improve mother’s health status before/during pregnancy, such as control of anemia and chronic energy malnutrition”. In December 1996, the complementary “Mother Friendly Movement” (*Gerakan Sayang Ibu*) program was launched, due to concern over slower than expected progress towards reducing the maternal mortality ratio. The two key elements of this program, “Mother-Friendly Communities” and “Mother-Friendly Health Care Facilities”, sought to link communities with health care facilities, in an effort to overcome a variety of interconnected obstacles, including poor access, lack of referrals, inadequate transportation, and low delivery attendance by trained personnel.

In early 1999, the MOH commissioned a review and recommendations exercise, conducted by JHPIEGO and supported by USAID, to suggest ways to further improve the current efforts to reduce maternal mortality. This renewed interest in developing policy and program interventions to reduce the high rate of maternal and also infant mortality in Indonesia will require a variety of innovative approaches and interventions, including effective preventive strategies that can be provided at the community level, such as multi-micronutrient supplementation.

Helen Keller International (HKI), therefore, proposes to carry out a **Supplementation with Multiple Micronutrients InTervention (SUMMIT) activity targeted at improving maternal micronutrient status on the island of Lombok, Nusa Tenggara Barat (NTB) province, where maternal and infant health indicators rank among the poorest in Indonesia.**

**The specific goals of the SUMMIT activity are to determine if daily multiple micronutrient supplementation during the prenatal period through 3 months post delivery will:**

- I. Reduce the frequency of maternal mortality**
- II. Reduce the proportion of low birth weight newborns**
- III. Reduce neonatal and infant mortality rates**

